#### Phase IIa procedures

2.3.2

Participants will complete two individual sessions—one prior to and one following the group sessions—and eight group sessions delivered weekly or biweekly over a 6–8-week period (Figure 3). The initial individual session will last approximately 60 min, followed by a 45–60-minute follow-up session. Prior to the first visit, dietitians will collect relevant medical history and laboratory data. During the initial session, dietary intake will be assessed using the modified UK Diabetes and Diet Questionnaire (UKDDQ) to inform individualized nutrition prescriptions (50). Throughout the intervention, facilitators will monitor behavioral changes related to meal planning, food preparation, and physical activity, using a standardized adherence scale ranging from 1 (never) to 5 (consistently) (51). Family members will be invited to selected group sessions, including introductory and healthy-eating sessions, to promote a supportive home environment and reinforce family-centered dietary practices.

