#### Phase IIa sample

2.3.1

A single-arm feasibility design will be used to enroll 30 adults with T2D. Eligible participants will (1) self-identify as Beninese; (2) be aged 40–65 years; (3) have a clinical diagnosis of T2D for at least one year; (4) have an HbA1c level >7% at enrollment; (5) have a family member willing to participate or provide ongoing support; and (6) be willing to commit to the study protocol and attend scheduled sessions. Participants will be recruited from the pool of 512 individuals who participated in Phase Ib. The sample size of 30 was selected in accordance with recommendations for pre-pilot and feasibility studies (43). The intervention will include two individual sessions (45–60 min each) and eight group sessions (90–120 min each). Sessions will be delivered by six trained dietitians or nutritionists, with each group of 10 participants assigned two facilitators experienced in health promotion, trained in MNT, and committed to maintaining protocol fidelity.

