**Figure 3 F3:**
[figure not shown]
Schematic diagram of the feasibility study for the new cultural tailored medical nutrition therapy.

To support future replication and scalability, feasibility and acceptability outcomes will be evaluated using the RE-AIM (Reach, Effectiveness, Adoption, Implementation, and Maintenance) framework (52). Feasibility indicators will include recruitment strategies, session attendance, retention rates, and facilitator fidelity assessed through session observations. Acceptability will be measured using participant-reported perceptions of cultural relevance, perceived benefits, and overall satisfaction. Although Phase IIa is not designed to test efficacy, exploratory assessments of behavioral and biomedical outcomes will be conducted at baseline and 12 weeks post-intervention. Dietary adherence will be assessed using a multi-method approach combining the Perceived Dietary Adherence Questionnaire (PDAQ) adapted to the Benin Food Guide (53), dietary intake from the modified UKDDQ, and facilitator-rated behavioral monitoring (e.g., meal planning, food preparation, and physical activity practices) (51). Family functioning will be measured using the McMaster Family Assessment Device (54), diabetes knowledge using the ADKnowl questionnaire (55), and self-efficacy using the Diabetes Self-Efficacy Scale (DSES) (56). Anthropometric and clinical measures, including weight, height, waist circumference, blood pressure, and HbA1c—will also be collected with informed consent. Qualitative feedback from participants and facilitators will be analyzed to identify themes related to communication, comprehension, engagement, and perceived cultural relevance. Transportation incentives will be provided to facilitate participation in sessions and follow-up assessments.

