#### Quantitative analysis: phase IIa

2.3.3

Descriptive statistics will be used to summarize participant characteristics and feasibility and acceptability outcomes. Changes in exploratory behavioral and biomedical outcomes between baseline and post-intervention will be analyzed using paired-samples *t*-tests, Wilcoxon signed-rank tests, or McNemar's tests, as appropriate. Exploratory analyses will examine associations between dietary adherence scores and biomedical indicators (HbA1c and anthropometric measures) to assess convergent validity. All analyses will be conducted using Stata (version 19; StataCorp LLC, College Station, TX, USA), with statistical significance set at *P* < 0.05.

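### The Phase IIa adherence raters belong to the staff who collect participants' laboratory data, so correlating their rating with HbA1c and body size can partly reflect what they already know

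*Protocol article*

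**What the plan says.** All references are to the protocol article.

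- **Design (2.3.1).** "A single-arm feasibility design will be used to enroll 30 adults with T2D". One entry criterion is to "have an HbA1c level >7% at enrollment", so an HbA1c value exists for everyone at entry.
- **Staff (2.3.1).** "Sessions will be delivered by six trained dietitians or nutritionists, with each group of 10 participants assigned two facilitators".
- **Data held before rating (2.3.2).** "Prior to the first visit, dietitians will collect relevant medical history and laboratory data".
- **Rating (2.3.2).** "Throughout the intervention, facilitators will monitor behavioral changes related to meal planning, food preparation, and physical activity, using a standardized adherence scale", scored from 1 to 5.
- **Place of the rating (2.3.2, after Figure 3).** Dietary adherence combines the PDAQ, "dietary intake from the modified UKDDQ, and facilitator-rated behavioral monitoring". Outcomes are taken at baseline and 12 weeks post-intervention.
- **Analysis (2.3.3).** "Exploratory analyses will examine associations between dietary adherence scores and biomedical indicators (HbA1c and anthropometric measures) to assess convergent validity". Significance is set at P < 0.05.

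**The concern.** A convergent-validity correlation is informative only if the measure and the criterion are obtained independently. Here the staff who produce one adherence component may already know the participant's laboratory values, and they see body size at every session. A facilitator who knows that glycemic control is poor, or who sees that a participant is heavy, may score that person lower without observing any difference in behavior. The rating then correlates with the criterion even if it carries no information on adherence. This is criterion contamination.

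At stake is how far the Phase IIa correlation can be trusted. If it includes the facilitator rating, a result in the expected direction could be read as support for the measure when it partly echoes the rater's prior information.

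**Working it through.** **Step 1. Are the raters the staff who collect the data?** Section 2.3.2 names dietitians for data collection and facilitators for rating. The staffing figures in 2.3.1 connect them: 30 participants / 10 per group = 3 groups, and 3 × 2 facilitators = 6. This reproduces the stated six dietitians or nutritionists, so raters and session staff are one group. The text does not say whether the person who collects a given participant's data also rates that participant.

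**Step 2. Is there masking?** None is described for Phase IIa. The blinding in 2.4.1 belongs to Phase IIb and concerns group allocation.

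**Step 3. Possible size.** The documents give no figures for this, so the following are assumptions:
- L = correlation of the rating with baseline HbA1c that arises only from rater knowledge, 0.2 to 0.5.
- ρ = correlation of baseline with 12-week HbA1c, 0.7 (range 0.5 to 1.0; the value 1.0 also covers use of baseline HbA1c itself).
- No true association; n = 30; Pearson test, two-sided 0.05 (the plan does not state sidedness).
- Composite = three equally weighted, mutually independent standardized components, only one of which is the rating.

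Critical |r| = t/√(28 + t²) with t = 2.048, which gives 0.361.

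Expected r with 12-week HbA1c is −Lρ for the rating alone and −Lρ/√3 for the composite. Simulated rates of P < 0.05 at ρ = 0.7 (200,000 studies per row):

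| L | r, rating alone | P < 0.05 | r, composite | P < 0.05 |
|---|---|---|---|---|
| 0.2 | −0.14 | 11% | −0.08 | 7% |
| 0.3 | −0.21 | 20% | −0.12 | 10% |
| 0.5 | −0.35 | 49% | −0.20 | 19% |

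Over ρ = 0.5 to 1.0 (20,000 studies per setting):
- Rating alone: 8–19% at L = 0.2, 12–37% at L = 0.3, 27–83% at L = 0.5.
- Composite: 6–9%, 7–15% and 12–34%.

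If the other two components correlate 0.5 with each other, the composite variance is 1 + 2 + 2 × 0.5 = 4. Then r = −Lρ/2, and at ρ = 0.7 the rates are about 6%, 8% and 15%. With L = 0 the simulated rate is 4.8–5.2%, as it should be.

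**Step 4. Direction.** Section 2.3.3 does not say which HbA1c is used. Take change = 12-week minus baseline, with both standardized. Its variance is (1 − ρ)² + (1 − ρ²) = 0.09 + 0.51 = 0.60, and its covariance with the rating is L(1 − ρ) = 0.3L. So r = 0.3L/√0.60 = +0.08 at L = 0.2 and +0.19 at L = 0.5. The sign reverses: participants with high baseline values are rated low but regress most. A significant negative r, the direction that would support validity, then occurs in only about 0.9% down to 0.2% of studies, against a nominal 2.5%.

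**The case against.** Several counter-arguments stand and limit the point.

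- **HbA1c is not named among the laboratory data.** The enrolment criterion means a value exists, but the text does not say that the dietitian holds it. Nor does it establish that collector and rater coincide for each participant. A reader might infer that the correlation *does* reflect rater knowledge; the documents show only that it *can*.
- **A reader might also infer that the bias persists, and flatters the measure, whatever criterion is chosen.** Step 4 shows otherwise: with change in HbA1c it works against apparent validity.
- **Only one of three components is affected.** A composite dilutes the effect, and the PDAQ or UKDDQ analyzed separately carries nothing from the facilitator rating. Section 2.3.3 speaks of scores without saying whether the rating enters alone, combined or at all.
- **No decision hangs on the result.** A reader might infer that a spurious correlation would carry the measure into Phase IIb. But readiness rests on feasibility and acceptability indicators above 75% (2.3), and sections 2.4.2 and 2.4.3 do not make the Phase IIb adherence outcome conditional on this correlation.
- **Access rules may sit in the full protocol.** An article can leave detail of that kind out.

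What does not fall away is the stated sequence: staff hold laboratory data, then rate, and the rating belongs to the adherence assessment whose scores are correlated with laboratory and body-size criteria.

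**Conclusion.** The point holds as a risk to an exploratory analysis. In Phase IIa any association of the facilitator rating, alone or within a composite, with HbA1c or anthropometry can partly reflect what the rater already knew, and nothing in the Phase IIa text guards against it. Against 12-week HbA1c with ρ = 0.7, the false-positive rate is about 11–49% for the rating alone and about 7–19% for an equal-weight composite of independent components, against 5%. These figures rest on assumed leakage of 0.2 to 0.5 and a rating with no true information; they show possible size and are not a forecast. The direction is not fixed until the plan says which HbA1c is used. This is a cheap improvement worth making, with no bearing on the Phase IIb progression criteria.

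**What to change.** In section 2.3.3:

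1. Report convergent validity separately for each adherence component.
2. Base the validity conclusion on the PDAQ as completed by the participant, and on the UKDDQ only if a facilitator does not administer it. Section 2.3.2 places a UKDDQ assessment in the first individual session, so who administers it needs stating.
3. Do not use the facilitator rating, or any composite that contains it, as validity evidence. If such a correlation is shown, report it descriptively and say that the raters were not masked to laboratory data.
4. State whether baseline, 12-week or change in HbA1c is the criterion.

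Withholding follow-up values from raters would add little: ratings are made during the intervention and the outcome HbA1c comes 12 weeks after it. Body size cannot be masked from staff who meet participants in person.

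The cost is a few sentences. Dietitians keep the data they need for counseling. The downside is that the facilitator rating gains no validity evidence from Phase IIa.

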**Figure 3 F3:**
[figure not shown]
Schematic diagram of the feasibility study for the new cultural tailored medical nutrition therapy.

To support future replication and scalability, feasibility and acceptability outcomes will be evaluated using the RE-AIM (Reach, Effectiveness, Adoption, Implementation, and Maintenance) framework (52). Feasibility indicators will include recruitment strategies, session attendance, retention rates, and facilitator fidelity assessed through session observations. Acceptability will be measured using participant-reported perceptions of cultural relevance, perceived benefits, and overall satisfaction. Although Phase IIa is not designed to test efficacy, exploratory assessments of behavioral and biomedical outcomes will be conducted at baseline and 12 weeks post-intervention. Dietary adherence will be assessed using a multi-method approach combining the Perceived Dietary Adherence Questionnaire (PDAQ) adapted to the Benin Food Guide (53), dietary intake from the modified UKDDQ, and facilitator-rated behavioral monitoring (e.g., meal planning, food preparation, and physical activity practices) (51). Family functioning will be measured using the McMaster Family Assessment Device (54), diabetes knowledge using the ADKnowl questionnaire (55), and self-efficacy using the Diabetes Self-Efficacy Scale (DSES) (56). Anthropometric and clinical measures, including weight, height, waist circumference, blood pressure, and HbA1c—will also be collected with informed consent. Qualitative feedback from participants and facilitators will be analyzed to identify themes related to communication, comprehension, engagement, and perceived cultural relevance. Transportation incentives will be provided to facilitate participation in sessions and follow-up assessments.

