The active intervention phase spans Months 0–6. Core group-based OSanDiaBé sessions (n = 8) and the first two individual MNT sessions are delivered during Months 0–3. Two monthly booster individual MNT sessions are delivered during Months 3–6. The maintenance phase (Months 6–12) involves no intervention contact and includes follow-up assessments only.

Outcome assessments for both groups will be conducted at baseline and at 3, 6, and 12 months. Dietary adherence will be assessed using a multi-method approach combining the PDAQ adapted to the Benin Food Guide, dietary intake from the modified UKDDQ, and facilitator-based behavioral monitoring, consistent with the Phase IIb measurement strategy (50, 51, 53). Secondary outcomes will include: diabetes knowledge assessed using the ADKnowl questionnaire (55); family functioning measured with the 12-item General Functioning subscale of the Family Assessment Device (54); nutrition self-efficacy assessed using the DSES (56); and quality of life measured with the EuroQol EQ-5D (59). Anthropometric measures (weight, height, body mass index, waist circumference) and metabolic indicators (blood pressure, HbA1c, lipid profile) will be collected, with venous blood samples analyzed at an accredited hospital laboratory. In addition, focus group discussions with participants and facilitators will be conducted at 3, 6, and 12 months to capture experiential feedback related to intervention delivery, cultural relevance, and perceived impact, and to inform future program refinement.

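### The dietary adherence measure includes a facilitator rating that names physical activity, so that component, and any composite containing it, can rise without dietary change and its association with HbA1c can partly reflect exercise

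*Protocol article*

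**What the plan says.** Section 2.3.2 (Phase IIa procedures) has facilitators score three behaviors on one five-point scale, where 1 is the lowest rating and 5 the highest: "facilitators will monitor behavioral changes related to meal planning, food preparation, and physical activity, using a standardized adherence scale". Later in the same section these ratings become part of the adherence measure. It opens "Dietary adherence will be assessed using a multi-method approach combining the Perceived Dietary Adherence Questionnaire (PDAQ) adapted to the Benin Food Guide", adds intake from the modified UKDDQ, and ends with "facilitator-rated behavioral monitoring (e.g., meal planning, food preparation, and physical activity practices").

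Section 2.3.3 then plans "associations between dietary adherence scores and biomedical indicators (HbA1c and anthropometric measures) to assess convergent validity".

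Section 2.4.2 carries the three-part measure into Phase IIb, "combining the PDAQ adapted to the Benin Food Guide, dietary intake from the modified UKDDQ, and facilitator-based behavioral monitoring", and cites the same source for the facilitator part. That section also names dietary adherence the primary behavioral outcome of Phase IIb. Nowhere does the article take the activity rating out of the adherence measure, and neither the text nor Table 2 lists physical activity as an outcome of its own.

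**The concern.** The Phase Ia model (section 2.1) makes dietary adherence the behavioral target and the route to better glycemic control. One of the three behaviors named for the facilitator rating lies outside that construct. A participant who becomes more active but eats as before can register a higher facilitator rating, and it would be reported as dietary adherence.

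The validity check adds to the problem. HbA1c and body measurements are outcomes that physical activity can move directly. If the activity item drives a correlation with them, the result would be read as evidence that the diet measure is valid, and that measure then serves as the Phase IIb primary behavioral outcome. The defect lies in what is rated and would remain whoever did the rating.

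**Working it through.** The article gives no figure to reproduce here, so the check is a reading of the definition followed by an illustration.

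**From the article.** Three sources (PDAQ, UKDDQ, facilitator rating); three behaviors named for the facilitator rating, one of them not dietary; scale 1 to 5; Phase IIa n = 30; significance at P<0.05.

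**Assumed, not in the article.** The facilitator score is the equally weighted mean of the three named behaviors. A composite, if formed, is the equally weighted mean of the three standardized sources. Diet has no effect on the biomedical measure, and activity correlates r = -0.2, -0.4 or -0.6 with it. Tests are two-sided.

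**1. Shift in the facilitator rating when only activity changes.**
- Activity 1 to 5: 4/3 = 1.33 points, or 1.33/4 = 33% of the scale range. This is the largest shift possible.
- Activity 2 to 4: 2/3 = 0.67 points, or 17% of the range.

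**2. Spurious correlation, independent items.** For a weighted sum with weights w, item correlation matrix R and item-outcome correlations c, the correlation with the outcome is w'c / √(w'Rw).
- Facilitator rating alone: (r/3)/√(1/3) = r/√3.
- Three-source composite: the standardized facilitator score contributes r/√3 and the other two sources contribute 0, so the result is (r/√3)/√3 = r/3.

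| Activity-outcome r | Facilitator alone | P<0.05, n = 30 | Composite | P<0.05, n = 30 |
|---|---|---|---|---|
| -0.2 | -0.12 | 9% | -0.07 | 6% |
| -0.4 | -0.23 | 22% | -0.13 | 11% |
| -0.6 | -0.35 | 48% | -0.20 | 19% |

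The percentages are simulated. The PDAQ alone stays at about 5%. With the activity item removed, both correlations are 0 under these assumptions.

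**3. Items that inter-correlate at 0.3 (assumed).** The two food items, the PDAQ and the UKDDQ now each correlate 0.3r with the outcome, through their link to activity.
- With the activity item: the facilitator score has correlation 0.730r. The composite is (0.730 + 0.3 + 0.3)r / √(3 + 2(0.3 + 2 × 0.411)) = 1.330r/2.290 = 0.581r.
- Without it: the facilitator score has 0.372r. The composite is (0.372 + 0.3 + 0.3)r / √(3 + 2(0.3 + 2 × 0.372)) = 0.972r/2.256 = 0.431r.
- For r = -0.2 and -0.4 the composite goes from -0.12 and -0.23 to -0.09 and -0.17. Removing the item takes away 1 - 0.431/0.581 = 26%. What remains is confounding between diet and activity, which no choice of items removes.

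**The case against.** The strongest reply is that the article gives no sum, mean or weight. It says only that three sources are combined, and section 2.3.3 speaks of scores in the plural, which fits three instruments reported side by side. Scoring detail can properly sit in a fuller document. This stands against any claim about size, and it means the PDAQ and UKDDQ results may be free of the problem. It does not answer the point about content: activity is named as part of the measure, and any positive weight on it has the effect described. The list is introduced as examples, but that does not exclude an item it names.

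Two further replies have force. Section 2.3.2 says Phase IIa is not designed to test efficacy, and the associations are exploratory in 30 people. Section 2.4.2 does not itself repeat physical activity. Its carry-over to Phase IIb is read from the same three-part description and the same cited source. The article also does not say how facilitators would rate wait-list controls, so whether a score containing the rating can be formed in both arms is unclear; that is a separate question.

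A reader might infer that the adherence-HbA1c link is partly an exercise effect, or that roughly a quarter to a half of such studies would be falsely significant. The documents support neither. The link can reflect exercise; nothing shows that it will. The 22% and 48% figures apply only if the facilitator rating alone is the score, items are independent and activity is related to the outcome at -0.4 or -0.6. Nor is the Phase IIb HbA1c comparison affected, since it is made by randomized arm. The Phase II analysis sections describe no mediation analysis through dietary adherence that could be distorted.

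**Conclusion.** The point holds in a limited form. The stated content of the dietary adherence measure includes a behavior that is not dietary. The facilitator rating and any composite containing it can therefore improve without dietary change, and their planned association with HbA1c and anthropometry cannot separate diet from exercise. The other two instruments, analyzed on their own, are unaffected.

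The ranges calculated above are illustrations that rest on the assumed weights and activity-outcome correlations; the article does not fix the true size. For the exploratory Phase IIa analysis the consequence is modest. The point deserves correction mainly because the same measure becomes the Phase IIb primary behavioral outcome.

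**What to change.** In section 2.3.2, and by reference in 2.4.2, state that only the dietary items of the facilitator rating (meal planning and food preparation) count toward dietary adherence. Report the physical activity rating as a separate lifestyle outcome, and keep it out of the dietary adherence scores used for the section 2.3.3 associations.

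The cost is one sentence. The same ratings are still collected, and the facilitator component has one item fewer. Because diet and activity may move together, the section 2.3.3 associations should still be read with that confounding in mind.
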